## **9.6 Concomitant care**

There will be no restrictions on concomitant care, which will be monitored carefully during the trial through the service use questionnaire (CA-SUS; Barrett et al., 2012).

# **10. Measures and outcomes**

## **10.1 Child outcomes**

The electronic version of this document is the latest version. It is responsibility of the individual to ensure that any paper material is the current version. Printed material is uncontrolled documentation.

### **10.1.1 Parent-rated behaviour problems**

*T1 covariate, sample description; mean difference at T2 as primary outcome; mean difference at T3, T4 and T5 as secondary outcomes.*

This will be measured with the ODD subscale of the Swanson, Nolan, and Pelham Rating Scale – the MTA version (SNAP-IV; Swanson et al., 2001). The subscale consists of eight items that are rated on a 4-point scale (not at all, just a little, quite a bit, very much). The subscale score is obtained by averaging responses across the eight items (i.e., summing the items and dividing by 8). This SNAP-IV ODD subscale is a valid outcome measure for use in clinical trials (Hall et al., 2020).

Child disruptive and defiant behaviour was selected as the primary outcome because for many parents of children referred to clinical services, this is likely to be the most urgent treatment target at the time of their initial referral.

### **10.1.2 Parent-rated hyperactivity/impulsivity and inattention**

*T1 covariate, sample description, mean difference at T2 and T5 secondary outcomes.*

This will be measured with the respective subscales of the SNAP-IV (Swanson et al., 2001). Each subscale of SNAP-IV consists of 9 items that are rated on a 4-point scale (not at all, just a little, quite a bit, very much). The subscale scores are obtained by averaging across the 9 items associated with the subscale (i.e., summing the items and dividing by 9) and can be further combined into a single ADHD scale score by deriving an average across the two subscales (i.e. summing the 18 items and dividing by 18) (Bussing et al., 2008; Hall et al., 2020) The SNAP-IV ADHD scale has confirmed validity for use as an outcome measure in clinical trials (Hall et al., 2020).

### **10.1.3 Parent-rated emotional problems**

*T1 covariate, sample description mean difference at T2 and T5 exploratory outcomes*

This outcome will be measured by the respective SDQ subscale (Goodman, 1997). This subscale measures fearfulness, anxiety and low mood and consists of 5 positively phrased items rated on a 3-point scale (not true, somewhat true, and certainly true). Individual items' scores are summed to derive an overall emotional problems subscale score. Baseline scores (T1) will be extracted from the medical records, and we will use information from the SDQ completed nearest to the baseline assessment due date. T2 and T5 data will be collected online via the Sealed Envelope platform. We acknowledge that it may not be possible to collect T2 data in this way for all participants who are already enrolled in the trial. Therefore, if feasible, we may also extract T2 data from the medical records, if a participant completed the SDQ as part of the routine clinical follow-up within the T2 visit window.

Please note: in OPTIMA, parents will complete the full SDQ measure, as the questionnaire license holder does not permit a single subscale use.

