## 8. Eligibility criteria

### 8.1 Inclusion Criteria

- Parents of all new referrals of children aged 5 years 0 months to 11 years and 11 months that have been accepted onto the assessment waiting list and their referred children. A 'new referral' is defined as a child who has been on a waiting list for assessment for no longer than nine calendar months. This will be confirmed through screening medical records.
- Parents aged 18 years or older: confirmed through screening.

The electronic version of this document is the latest version. It is responsibility of the individual to ensure that any paper material is the current version. Printed material is uncontrolled documentation.

- Child screened positive for high levels of hyperactivity/impulsivity, inattention, and conduct problems: Child scored  $\geq 8/10$  on the hyperactivity/inattention and  $\geq 4/10$  on the conduct problems subscale of the SDQ, established through screening medical records. These cut-offs identify the top 10% of the population (Youth In Mind)
- English language competence: parent confirms through screening.
- Access to a STEPS compatible mobile device (iOS 9.0 or later; Android 4.1 or later) with access to the internet (i.e., mobile internet or wi-fi); parent confirms through screening.

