|                                  |  |  |   |  |  |  |  |   |   |   |   |
|----------------------------------|--|--|---|--|--|--|--|---|---|---|---|
| PSCS                      |  |  | X |  |  |  |  | X |   |   | X |
| CGSQ                      |  |  | X |  |  |  |  | X |   |   | X |
| CHU9D                     |  |  | X |  |  |  |  | X | X | X | X |
| EQ-5D-5L                  |  |  | X |  |  |  |  | X | X | X | X |
| CA-SUS                    |  |  | X |  |  |  |  | X | X | X | X |
| ESO child assent          |  |  | X |  |  |  |  | X |   |   | X |
| ESO                       |  |  | X |  |  |  |  | X |   |   | X |
| CODSS                     |  |  | X |  |  |  |  | X |   |   | X |
| APP USAGE:                |  |  |   |  |  |  |  |   |   |   |   |
| Number of completed steps |  |  |   |  |  |  |  |   |   |   |   |
| Other app usage events    |  |  |   |  |  |  |  |   |   |   |   |
| Trial expectations        |  |  | X |  |  |  |  |   |   |   |   |
| Experience of parenting   |  |  | X |  |  |  |  | X | X | X | X |
| Adverse events (MAPED)    |  |  | X |  |  |  |  | X | X | X | X |
| Pharmacological treatment |  |  |   |  |  |  |  |   |   |   | X |
| Clinical diagnosis        |  |  |   |  |  |  |  |   |   |   | X |
| Qualitative interviews    |  |  |   |  |  |  |  |   |   |   |   |

\*T1 SDQ emotional subscale scores will be extracted from the child's medical records, T2 and T5 SDQ will be complete online via the Sealed Envelope platform.

HIC = high levels of hyperactivity/impulsivity, inattention and conduct problems; LAC = child in local authority care; SCQ = The Social Communication Questionnaire; CCBS = Child's Challenging Behaviour Scale version 2; SNAP-IV = The Swanson, Nolan, and Pelham Rating Scale – the MTA version; ODD = Oppositional Defiant Disorder; ADHD = Attention/Deficit-Hyperactivity Disorder; SDQ = Strengths and Difficulties Questionnaire; CPRS-SF = The Child-Parent Relationship Scale- Short Form; PS = The O'Leary Parenting Scale; PSCS = The Parental Sense of Competence Scale; CGSQ = The Caregiver Strain Questionnaire; CHU9D = Child Health Utility; CA-SUS = The Child and Adolescent Service Use Schedule; MAPED = Medical and psychological events and difficulties questionnaire; CODSS = Child Oppositional and Defiance Speech Sample Scale; ESO = Etch-a-Sketch Online.

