#### **14.2 Method 2: Interactive CAMHS Assessment Network (ICAN)**

In North East London NHS Foundation Trust, routine outcome measures are collected through the Interactive CAMHS Assessment Network (ICAN). It is a digital application in which clinicians, young people, parents, caregivers, and teachers can provide routine clinical measures. ICAN provides useful feedback to clinicians to help track progress and data in real-time and is directly linked to the electronic patient record.

Parents of newly accepted referrals, who provide consent for research contact through ICAN, will be asked to complete the SDQ also through ICAN. This information will be then passed onto the research team, who will review the SDQ scores to establish eligibility. Parents of children who meet eligibility criteria will be approached by the researcher with an invitation to take part (by email, phone or post). Once a parent expresses an interest in taking part, a researcher will arrange a phone call to take the parent through the study details and the rest of the procedure will be identical to that described for participants identified through MHE (see 'Method 1: myHealthE portal').

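### The rule for the baseline SDQ emotional score does not require the record to precede randomisation, so read literally it can admit a post-randomisation score as the covariate (minor; one exploratory outcome)

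*Protocol*

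**What the plan says.** Section 10.1.3 gives the SDQ emotional score its role in the italic line under the heading: "T1 covariate, sample description mean difference at T2 and T5 exploratory outcomes". The T1 value is not collected by the trial. "Baseline scores (T1) will be extracted from the medical records", and where the record holds more than one form, "we will use information from the SDQ completed nearest to the baseline assessment due date". The footnote to Table 2 repeats the source without a date limit: "T1 SDQ emotional subscale scores will be extracted from the child's medical records".

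The same section says that online collection at T2 may not be possible "for all participants who are already enrolled in the trial". It therefore allows T2 scores to come from the records as well, "if a participant completed the SDQ as part of the routine clinical follow-up within the T2 visit window". According to the revision history, this outcome was added in version 2.2 of July 2022. Section 12 has recruitment starting in January 2022.

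Four other places bear on timing:

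- Section 6 schedules T1 within one month before randomisation.
- Section 15 randomises only after the baseline assessments are complete.
- Section 8.1 establishes eligibility from an SDQ already in the records, for a child who "has been on a waiting list for assessment for no longer than nine calendar months".
- Section 17 opens each assessment window two weeks before the scheduled date and closes it four weeks after.

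Section 19.1 applies models similar to the primary ANCOVA to the other continuous secondary and exploratory scores. Its bracketed list does not name the emotional score, but section 10.1.3 labels that score a T1 covariate.

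**The concern.** Nearest is a two-sided criterion. It measures distance from the due date and takes no account of whether the form came before or after randomisation. For a trial assessment this would not matter, because section 15 makes baseline completion a condition of randomisation. Here the score is picked out of routine records. For families enrolled before version 2.2 it may be picked months later, when further forms may already be on file.

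If a post-randomisation form is taken as T1 for a family in the STEPS arm, the covariate may already carry part of the treatment effect, and adjusting for it removes that part from the estimate. The T1 value is also used to describe the sample, so a later score would be reported as a baseline characteristic. If T2 is taken from the records too, nothing stops the same form from filling both slots.

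**Working it through.** **The plan's own figure.** No sample size, correlation or effect is stated for the SDQ emotional score. The only figure available is the primary one (section 13). With d = 0.4, two-sided alpha 0.05 and 90% power, n per arm = 2 × (1.960 + 1.282)² / 0.4² = 131.3, rounded up to 132. Then 132 / (1 − 0.25) = 176 per arm, 352 in total. This reproduces exactly, uses SNAP-IV ODD only, and does not depend on the point made here.

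**When can a later form be the nearest?**

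- The due date lies 0 to 1 month before randomisation (section 6).
- The T2 window opens about 2.5 months after randomisation and closes about 4 months after it (section 17).
- A form from the opening of that window is therefore 2.5 + 0 = 2.5 to 2.5 + 1 = 3.5 months from the due date. One from its close is 4 to 5 months away.
- The rule picks the later form whenever the eligibility SDQ is further from the due date than that. The threshold is roughly 3 months at the opening of the window and 4 to 5 months at its close.
- A child may have waited up to nine months (section 8.1), so an eligibility SDQ of that age is possible. How common it is cannot be read from the protocol.

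**Size of the bias.** Let tau be the true effect, beta the ANCOVA slope on the covariate, f the share of children whose T1 form is post-randomisation (taken as equal in both arms), and g the share of tau already present in that form. The arm difference in the covariate is then f × g × tau, and the adjusted estimate is

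tau − beta × (f × g × tau) = tau × (1 − beta × f × g).

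The protocol gives none of beta, f or g. Assuming beta from 0.4 to 0.8 and g from 0.5 to 1:

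| f | lowest (beta 0.4, g 0.5) | highest (beta 0.8, g 1) |
|---|---|---|
| 5% | 0.4 × 0.05 × 0.5 = 1% | 0.8 × 0.05 × 1 = 4% |
| 10% | 2% | 8% |
| 20% | 4% | 16% |

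**Check by simulation.** The settings were 400,000 children per scenario, tau = −0.4 SD, a correlation of 0.6 between the pre-randomisation score and the outcome, and 0.75 between the later score and the outcome. All are assumptions. Attenuation was 2.8% (g = 0.5) and 5.3% (g = 1) at f = 10%, and 7.4% and 14.0% at f = 20%. With beta = 0.6 the formula gives 3% and 6%, then 6% and 12%. The two agree within Monte Carlo error of about 1 to 2 percentage points. Where the mis-selected form was also the T2 form, attenuation was about 7% at f = 10% and about 14% at f = 20%.

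**Against sampling error.** With 132 analysed per arm and a correlation of 0.6, the standard error is √(2 × (1 − 0.36) / 132) = 0.098 SD. At f = 10%, beta = 0.6, g = 1 and a true effect of 0.4 SD (borrowed from the primary outcome for scale), the shift is 0.06 × 0.4 = 0.024 SD, about a quarter of a standard error.

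**The case against.** The best reply is that the sentence governs a score labelled baseline and T1. The protocol places T1 before randomisation in section 6, in Table 2 and in section 15, so the natural reading is the closest form before randomisation. That is probably what was intended, and it is why this is a wording fault and not a design fault. It does not remove the point: those sections schedule trial assessments and do not limit the dates of routine records, while section 10.1.3 states its own selection rule.

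The second reply is that the route is narrow. It needs both an old eligibility SDQ and a routine SDQ after randomisation. This stands, in three respects:

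- A reader might take the nine months in section 8.1 as the age of the SDQ. It is the longest permitted time on the waiting list, and the screening form may be much more recent.
- A reader might infer that all sites repeat the SDQ. Section 14.2 describes routine outcome measures at one trust and says "ICAN provides useful feedback to clinicians to help track progress and data in real-time", but not that the SDQ is repeated.
- Section 9.4 expects no clinical assessment in the first three months. Digital SDQ collection does not depend on an assessment, and section 10.1.3 itself provides for routine forms in the T2 window, though conditionally.

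Third, a form completed soon after randomisation would carry little of the effect of a self-paced, three-month app. That is fair, and it is why g below 1 belongs in the range.

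**Conclusion.** The point holds as a minor one. The selection rule as written allows a post-randomisation SDQ to serve as the covariate, and allows one form to serve as both T1 and T2. If that happened and STEPS had an effect by then, the estimate for this exploratory outcome would be biased toward no effect. It could not manufacture a benefit through this mechanism.

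The size rests wholly on assumed values of beta, f and g and on equal mis-selection in the two arms: about 1–4% at f = 5%, 2–8% at 10% and 4–16% at 20%. If mis-selection is rare, the bias is negligible beside the sampling error.

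Two stronger readings are tempting and are not supported. One is that the plan will shrink the effect substantially. The documents give no basis for a large share of mis-selected baselines, nor for the full effect being present in them. The other is that mis-selection would differ by arm through differing clinical contact. No section indicates that routine SDQ completion differs between STEPS and WAU.

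The primary outcome, the secondary outcomes, the SNAP-IV baselines and the sample size of 352 are untouched.

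**What to change.** In section 10.1.3, replace the selection rule with: *the most recent SDQ completed on or before the date of randomisation*. Record the completion date with the score, and add that no form may serve as both T1 and T2. Carry the same limit into the footnote to Table 2.

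The eligibility SDQ required by section 8.1 should supply such a form for every child. With the rule in place f = 0, so the attenuation described here is zero.

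The cost is one or two sentences and a date check at extraction. No new data are needed and the sample size does not change. The downside is that some baseline scores will be older than under the present rule and slightly less predictive of the outcome, with a small loss of precision.

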### **10.1.4 Independent observer-rated behaviour problems.**

*T1 covariate, mean difference at T2 and T5 as exploratory outcomes.*

The electronic version of this document is the latest version. It is responsibility of the individual to ensure that any paper material is the current version. Printed material is uncontrolled documentation.

Parents and children will jointly complete an online drawing task, Etch-a-Sketch Online (ESO; Oliver & Pike, 2021). It is a novel and validated online tool that allows remote observation of parent-child interactions at home. During the task lasting 5 minutes, parents and children will take turns drawing a simple picture on a mobile phone screen. The task will be audio recorded and the parent-child verbal exchange will be rated using the Child Oppositional and Defiance Speech Sample (CODS). This captures the level of four problematic aspects of child behaviour (i.e., being argumentative, defiant, easily annoyed, angry) by an independent observer (a member of the research team) using a 5-point scale (not at all, a little, moderately, very, extremely). The observers will be provided with a set of rating instructions and the rating process will be calibrated using a subset of 5 audio recordings before the rest of the rating is completed. Agreement between observers will be monitored on regular basis. The overall rating score will be derived by averaging across the 4 items corresponding to target behaviours (i.e., summing the items and dividing by 4).

## **10.2 Parent/family outcomes**

### **10.2.1 Parenting style: laxness**

*T1 covariate, mean difference at T2 and T5 as secondary outcomes.*

Laxness captures a lack of consistent responding with confirmed validity (Rhoades & O'Leary, 2007). This will be measured with a 5-item subscale from The O'Leary Parenting Scale or PS (Arnold, O'Leary, Wolff, & Acker, 1993). Probabilities of using specific discipline strategies in response to child misbehaviour are rated on a 7-point scale and are anchored by one effective and one ineffective response strategy. Responses to individual items are summed up to derive an overall subscale score.

### **10.2.2 Parenting style: over-reactivity**

*T1 covariate, mean difference at T2 and T5 secondary outcomes.*

Over-reactivity will be measured with a 5-item subscale from The O'Leary Parenting Scale (Arnold et al., 1993), which is a valid outcome measure that captures overly emotional or harsh responding (Rhoades & O'Leary, 2007). This See 'Parenting style: laxness' for information about responding and scoring.

### **10.2.3 Parenting satisfaction**

*T1 covariate, mean difference at T2 and T5 as secondary outcomes*

This outcome reflects domain-general parenting self-efficacy and satisfaction and will be measured with an 8-item subscale from the Parental Sense of Competence Scale (PSCS; Johnston & Mash, 1989). The items are positively and negatively framed, and parents make responses on a 6-point scale, with options ranging from "strongly disagree" to "strongly agree". The subscale score is calculated for each participant by summing up individual item scores. This subscale has good validity (Ohan, Leung, & Johnston, 2000).

### **10.2.4 Parenting efficacy**

*T1 covariate, mean difference at T2 and T5 secondary outcomes*

This outcome reflects the degree of anxiety, frustration, and motivation associated with the parental role and will be measured with an 7-item subscale from The PSCS (Johnston & Mash, 1989). For information about

calculating a subscale score see 10.2.4. 'Parenting satisfaction'. The validity of this subscale remains unclear (Ohan et al., 2000).

### **10.2.5 Parenting-related strain**

*T1 covariate, mean difference at T2 and T5 as secondary outcomes.*

This will be measured with the global score obtained on the Caregiver Strain Questionnaire (CGSQ; Brannan, Heflinger, & Bickman, 1997). CGSQ consists of 21-items with responses made on a 5-point Likert scale ranging from "not at all" to "very much". Three indices are calculated for each participant by averaging individual item scores for the three subscales: Objective Strain (11 items), Subjective Internalised Strain (6 items) and Subjective Externalised Strain (4 items). Global Caregiver Strain Score is determined by calculating the sum of the three subscale scores. The scale is a reliable and valid measure of parenting-related strain (Brannan et al., 1997).

### **10.2.6 Closeness of the child-parent relationship**

*T1 covariate, mean difference at T2 and T5 as secondary outcomes.*

This will be measured with the closeness subscale of the Child-Parent Relationship Scale – Short Form (CPRS-SF; Pianta, 1992). This 7-item subscale scale measures the extent to which parents feel that their relationship with a child is characterized by warmth, affection, and open communication that has good validity for measuring child-parent closeness (Driscoll & Pianta, 2011). Responses are made on 5-point Likert scale ranging from "definitely does not apply" to "definitely applies". The items are summed to obtain a single subscale score.

## **10.3 Other measures**

### **10.3.1 Characterisation of the child's behaviour problems**

*T1 sample description.*

This will be measured with the Child's Challenging Behaviour Scale version 2 (CCBS; Bourke-Taylor, Pallant, & Law, 2014). The CCBS is a 9-item measure of challenging behaviours for children aged 5-18 years. Parents rate agreement with statements about their child behaviour on a 4-point scale ranging from "strongly agree" to "strongly disagree", and the total score on the CCBS is calculated by summing the scores.

### **10.3.2 Autism spectrum disorder (ASD) symptoms**

*T1 sample description.*

This will be measured with the Social Communication Questionnaire – lifetime version (SCQ; Berument, Rutter, Lord, Pickles, & Bailey, 1999). The SCQ is a 40-item screening measure for autism spectrum disorder and is validated to use for ages 4 years and above. Questions focus on behaviours that are likely to be observed by the primary caregiver and concern the following domains: reciprocal social interactions, language and communication and repetitive and stereotyped patterns of behaviours. The presence of autism-positive behaviour is coded as 1 and its absence as 0. The first question concerns the level of current language and is not included in the total score. For children with language all questions apply, and the

The electronic version of this document is the latest version. It is responsibility of the individual to ensure that any paper material is the current version. Printed material is uncontrolled documentation.

maximum score is 39; for children without language, the first 6 questions do not apply so the maximum score is 33 (language items are inapplicable).

